**FIGURE 1 F1:**
[figure not shown]
Overview of the study timeline, including screening, intervention, and follow-up phases. This schematic illustrates the flow of participant activities and data collection across all phases of the study. Screening and baseline evaluations (Day 0) include eligibility verification, informed consent, structural MRI, and administration of behavioral questionnaires (YFAS 2.0, T-FCQ, CESD-R). The intervention phase (Days 1–7) involves daily tACS, with EEG performed on Days 1, 5, and 7, and behavioral assessments (S-FCQ, FCI, Go/No-Go task) performed on Days 1, 5, and 8. An fMRI will be performed post-tACS on Day 2. Post-intervention imaging (fMRI) and follow-up behavioral measures occur on Day 8. A follow-up assessment on Day 15 evaluates potential sustained effects and adverse events.

Secondary outcomes will focus on neural mechanisms underlying these behavioral changes. EEG will be recorded immediately before and after stimulation on Days 1, 5, and 7 to capture neurophysiological aftereffects (Figure 1). Key EEG parameters include frequency-specific power changes indicative of entrainment, phase-locking value (PLV), and event-related potentials (ERPs). Data will be analyzed at both sensor and source levels using established pipelines.

Functional magnetic resonance imaging will be used to assess changes in functional connectivity within craving-related neural networks. Imaging will be conducted pre- and post-intervention (Day 0 and Day 8) and will include both resting-state scans and a cue-reactivity paradigm (Figure 1). Connectivity will be examined using seed-based correlation and independent component analysis (ICA), targeting the impulsive (ACC), reflective (DLPFC), and interoceptive (insula) systems, which correspond to the stimulation targets.

Craving-related traits will be assessed using the T-FCQ and the YFAS 2.0, administered at baseline (Day 0), and again during follow-up (Day 15) (Figure 1). These measures will provide a broader understanding of individual differences in craving susceptibility and their potential modulation by tACS.

Finally, follow-up assessments on Day 15 will evaluate whether observed behavioral and neural changes persist beyond the immediate intervention phase. This longitudinal component is designed to assess the sustainability of tACS effects and explore delayed neuroplastic adaptations.

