#### 2.2.5 Sample size and power considerations

The sample size was calculated based on prior studies investigating neuromodulation effects on craving-related behavior and oscillatory activity (Song et al., 2019, 2022; Althubaiti, 2022; Kim et al., 2023; Gairola et al., 2024; Arifin and Yaacob, 2025; Sánchez-Garrido Campos et al., 2025). Assuming a moderate effect size (Cohen’s f = 0.25), an alpha level of 0.05, and a desired power of 0.80, a minimum of 35 participants per group is required to detect statistically significant differences in the primary behavioral outcome.

To account for potential attrition and non-compliance, a 20% dropout rate was incorporated into the calculation, yielding a final target of 175 participants distributed across the five study groups. This includes 140 participants in the FA+ parallel groups and 35 in the FA- crossover group.

Given the multimodal nature of data collection, including repeated electroencephalography (EEG) and functional magnetic resonance imaging (fMRI) measurements, a sensitivity analysis was also conducted. This analysis confirmed that the study remains adequately powered to detect within-subject changes in neural and behavioral outcomes while maintaining sufficient statistical power for between-group comparisons.

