### 2.3 Intervention

Participants will receive tACS targeting one of three cortical regions: the ACC, DLPFC, or insula. These targets were selected based on their involvement in the triadic model of craving, representing the impulsive, reflective, and interoceptive systems, respectively (Christie and Bechara, 2020).

Stimulation will be delivered at fixed frequencies supported by the literature on oscillation-specific effects of tACS. The DLPFC will be stimulated at 10 Hz (alpha frequency), while the ACC and insula will receive 6 Hz (theta frequency) stimulation. This frequency choice aligns with prior findings suggesting functional specificity of alpha oscillations in top-down control and theta oscillations in cognitive conflict and interoception (Stecher et al., 2021; Vogeti et al., 2022; Wischnewski et al., 2023).

The stimulation intensity will vary by region, reflecting anatomical depth and field modeling data. For the DLPFC and ACC, the peak-to-peak current will range between 1.5 and 2 mA. However, due to its deeper cortical location, the insula will be stimulated with higher intensities, between 8 and 9 mA peak-to-peak. This is consistent with recent human studies demonstrating the feasibility and tolerability of higher-output tACS for reaching deep brain structures (Shan et al., 2023; Wischnewski et al., 2023). All sessions will last 20 min and occur once daily over seven consecutive days.

Individualized modeling will be conducted using T1-weighted structural MRI scans to generate finite element models (FEMs). Electrode montages will then be optimized using ROAST (Realistic vOlumetric Approach to Simulate Transcranial electric stimulation) (Huang et al., 2019), allowing simulation of electric field distributions within each participant’s head. The modeling will ensure that target field strengths exceed 0.4 mV/mm, a threshold associated with effective neuromodulation (Wischnewski et al., 2023). If predicted intensities fall below this threshold in any region, montage adjustments will be implemented prior to stimulation. HD-Explore, an online visualization tool, will be used to confirm current flow patterns and facilitate replication by other researchers.

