### 2.5 Data collection and analysis

Behavioral data will be collected at multiple time points to evaluate the impact of tACS on food cravings and inhibitory control. The S-FCQ, FCI, and Go/No-Go task will be administered pre- and post-stimulation on Days 1 and 5, and again on Day 8 to assess short-term changes in craving and impulse regulation (Figure 1). Broader trait-level assessments, including the YFAS 2.0 and the T-FCQ, will be administered at baseline (Day 0) and again during the follow-up session on Day 15 to examine long-term or sustained effects (Figure 1).

Electroencephalographic data will be recorded on Days 1, 5, and 7 (Figure 1) using a 64-channel dry electrode cap following the international 10–20 system. Each EEG session will include 5 min of resting-state recording with eyes open, followed by 5 min of viewing food-related and neutral images. Recordings will be conducted both before and after stimulation to detect aftereffects. EEG data will be acquired using the ANT Neuro system at a sampling rate of 1064 Hz. Impedance will be maintained below 10 kΩ. Signal preprocessing and artifact correction will be performed using standard pipelines in EEGLAB and custom MATLAB scripts. Key neural indices will include spectral power, PLV, and ERPs.

Functional MRI data will be acquired using a Siemens 3T Prisma scanner with a 64-channel head coil. Imaging sessions will occur at baseline (Day 0), immediately post-tACS on Day 2, and again post-intervention (Day 8) (Figure 1). Each session will include an 8-min resting-state scan and a cue-reactivity task involving the passive viewing of highly palatable food and neutral images. The cue task will use a block design format with craving intensity ratings collected after each block. BOLD signal changes will be analyzed using Statistical Parametric Mapping 12 (SPM12) and FMRIB Software Library (FSL), with preprocessing steps including realignment, normalization, and spatial smoothing. Functional connectivity will be assessed using seed-based correlation and ICA approaches, focusing on DLPFC, ACC, and insula as predefined regions of interest.

All adverse events or discomforts related to tACS will be monitored daily throughout the intervention phase. Any participant experiencing persistent adverse effects will be withdrawn from the study and referred for appropriate follow-up care.

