By combining high-resolution EEG and fMRI, this study is positioned to provide a multimodal characterization of how tACS influences both oscillatory activity and large-scale network interactions. EEG will allow for the assessment of immediate entrainment and aftereffects, including changes in spectral power, PLV, and ERPs. fMRI, in turn, will assess the spatial and functional reconfiguration of networks via seed-based connectivity and independent component analysis. Particular attention will be paid to connectivity within and between the DLPFC, ACC, insula, amygdala, and striatum. It is expected that alpha-band tACS applied to the DLPFC will enhance top-down control and strengthen connectivity with subcortical structures involved in rewards regulation, while theta-band stimulation of the ACC and insula may normalize aberrant activity in the impulsive and interoceptive systems. This convergence of oscillatory and connectivity-based evidence may validate tACS as a network-level intervention for food craving regulation.

Moreover, the integration of behavioral data, including validated craving questionnaires and Go/No-Go task performance, will allow for a direct correlation between neurophysiological changes and observable cognitive and affective outcomes. The inclusion of both trait- and state-level craving assessments (T-FCQ, S-FCQ, FCI) strengthens the design by capturing both enduring tendencies and momentary fluctuations in craving behavior. When combined with EEG and fMRI findings, these behavioral metrics will provide a comprehensive, multidimensional index of tACS efficacy.

Despite these strengths, several limitations warrant consideration. The relatively brief intervention duration of seven sessions may not fully capture the long-term potential of tACS to modify eating behaviors. Longitudinal studies with extended intervention periods are needed to examine the durability of neural and behavioral changes. Furthermore, individual variability in tACS responsiveness remains a challenge. Factors such as baseline oscillatory state, cortical anatomy, and skull conductivity can influence current distribution and entrainment efficacy (Saturnino et al., 2017). Although individualized modeling using structural MRI and the ROAST pipeline will optimize electrode placement and predict electric field strength, future research should explore real-time, closed-loop tACS protocols tailored to ongoing neural dynamics.

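### All EEG is recorded before or after stimulation, so it can show aftereffects but not the entrainment that Section 2.4 and the Discussion attribute to it

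*Protocol article*

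**What the plan says.** The protocol article fixes the EEG schedule twice, each time with its purpose. Section 2.4: "EEG will be recorded immediately before and after stimulation on Days 1, 5, and 7 to capture neurophysiological aftereffects". Section 2.5: "Recordings will be conducted both before and after stimulation to detect aftereffects". Section 2.5 also gives the content of a recording: "Each EEG session will include 5 min of resting-state recording with eyes open, followed by 5 min of viewing food-related and neutral images". Stimulation is described separately in Section 2.3: "All sessions will last 20 min and occur once daily over seven consecutive days".

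Two statements go beyond that schedule. In Section 2.4, directly after the sentence on timing, the article says: "Key EEG parameters include frequency-specific power changes indicative of entrainment, phase-locking value (PLV), and event-related potentials (ERPs". In the Discussion it says: "EEG will allow for the assessment of immediate entrainment and aftereffects, including changes in spectral power, PLV, and ERPs".

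Section 2.5 plans linear mixed-effects models for the EEG parameters.

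**The concern.** Entrainment means that ongoing brain activity aligns to the applied current while that current is flowing. It can be observed only by recording during stimulation and dealing with the stimulation artifact. The schedule contains no such recording, and the artifact correction named in Section 2.5 is a standard pipeline with nothing specific to tACS.

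The Discussion names entrainment and aftereffects as two things that EEG will assess, and the design samples only the second. Entrainment is also the article's main argument for tACS: the Introduction uses it to set tACS apart from tDCS and rTMS, and the Discussion calls it a unique advantage. If the wording stands, a post-minus-pre power change could be presented as evidence that the rhythm was entrained, when the data cannot tell that apart from a change that arose by another route.

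**Working it through.** There is no figure in the plan to reproduce. The check sets the schedule beside the claims and asks what each comparison can identify.

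**Coverage of stimulation by EEG (FA+ participant)**
- EEG days: 3 (Days 1, 5 and 7; Sections 2.4 and 2.5).
- Recordings per EEG day: 2 (before and after).
- Length of a recording: 5 + 5 = 10 min (Section 2.5), assuming that the full block is run both times.
- Total EEG: 3 × 2 × 10 = 60 min. If the 10-minute block were instead split across the two recordings, the total would be 3 × 10 = 30 min.
- Total stimulation: 7 × 20 = 140 min (Section 2.3).
- Overlap as described: 0 of 140 min under either assumption.

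**What the comparisons can identify**

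Write Δ(band, arm) for the post-minus-pre change in power in a band.

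1. Δ within one active arm mixes any stimulation effect with drowsiness, time on task and repeated viewing of images.
2. Δ(active) − Δ(sham) largely removes those three. FA+ participants are randomized to an active arm or sham (Section 2.1), sham is meant to mimic the sensations of active stimulation (Section 2.3), and no arm is given a different EEG schedule.
3. What remains in step 2 is an effect of the current on activity after it stops. Plasticity can produce that with or without entrainment during the current. Entrainment can also occur and end with the current, leaving nothing to record. The contrast therefore cannot separate the two.

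**Frequency specificity**

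Each site has a single frequency: DLPFC 10 Hz, ACC 6 Hz, insula 6 Hz (Sections 2.1 and 2.3). A rise in the stimulated band against sham could be part of a broader change in power. The contrast that addresses this is:
- DLPFC arm: [Δ(alpha) − Δ(theta)] in active minus [Δ(alpha) − Δ(theta)] in sham.
- ACC and insula arms: [Δ(theta) − Δ(alpha)] in active minus [Δ(theta) − Δ(alpha)] in sham.

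This is the arm-by-band-by-time term of a mixed model. It uses recordings already planned.

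**Reach**

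Section 2.2.5 sizes the trial on the primary behavioral outcome ("Assuming a moderate effect size (Cohen’s f = 0.25), an alpha level of 0.05, and a desired power of 0.80"). EEG timing does not enter that calculation. The same section reports a sensitivity analysis covering neural outcomes but gives no figure for it, so the power of the three-way term is not stated.

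**The case against.** The strongest reply is that the operative text is right. Both Methods statements on timing give aftereffects as the purpose. The stronger phrase, that entrainment will be assessed, occurs only in the Discussion, and the Section 2.4 phrase claims an indirect sign rather than a measurement. The aim, objectives and secondary outcomes speak of modulating or altering oscillations, which pre/post EEG can address, so no listed endpoint requires entrainment to be shown. Much of this stands. It confines the problem to interpretation, but does not remove it: the schedule is stated in full, twice, and the claims exceed it, so this is not detail left to a fuller document.

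A reader might infer more than the article supports:
- **That a power change could just as well be drowsiness, time on task or repeated viewing.** This holds for a change within one arm. Against randomized sham these are largely controlled; plasticity is the rival that remains.
- **That PLV is meaningless once the current is off.** The article never says that PLV is referenced to the stimulation current. The Discussion links phase-locking to connectivity, which fits coupling between regions.
- **That the sponsor will report a positive change as proven entrainment, or a null change as failed entrainment.** The article does not say so. The wording leaves both readings open.

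It can also be said that the band contrast does not resolve entrainment versus aftereffect. That is correct. The contrast supports only a claim that an aftereffect is selective for a band.

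**Conclusion.** The point holds as a mismatch between the stated recording schedule and the stated inference. As described, EEG covers none of the 140 minutes of stimulation and can show only offline aftereffects. A post-minus-pre change against sham may be compatible with earlier entrainment but does not measure it.

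The consequence is limited to a secondary, mechanistic outcome, although it concerns the mechanism on which the rationale rests. Nothing here bears on the primary behavioral outcomes, the sample size or the error rates.

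The conclusion assumes that no EEG is taken during stimulation beyond what the article describes, that the EEG schedule is the same in all FA+ arms, and that sham is experienced as similar enough to active stimulation for non-specific effects to cancel.

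**What to change.** 1. In Section 2.4 and the Discussion, describe the EEG measures as aftereffects at the stimulation frequency, remove the entrainment wording, and state that entrainment will not be inferred from them.
2. Call an aftereffect frequency-specific only if the change in the stimulated band, relative to sham, exceeds the change in the non-stimulated band, tested by the arm-by-band-by-time term in the mixed model that Section 2.5 already plans. Theta and alpha power are then computed in every FA+ arm. This is a minimum condition: with one frequency per site, it cannot show that another frequency at the same site would have acted differently.

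If the sponsor wishes to keep the entrainment claim, the alternative is to specify EEG during stimulation together with a method for removing the stimulation artifact.

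The first change costs only wording, and the second adds one model term and no data. The price is a narrower mechanistic conclusion and reliance on an interaction test whose power is not stated, so a non-significant term should not be read as evidence that specificity is absent.

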### 2.4 Outcome measures

The primary outcomes of this study are changes in food craving intensity and inhibitory control following the tACS intervention. Craving will be assessed using the State Food Craving Questionnaire (S-FCQ) and the Food Craving Inventory (FCI), both administered before and immediately after stimulation sessions on Days 1 and 5 (Figure 1). Inhibitory control will be evaluated using a computerized Go/No-Go task at the same time points. These behavioral measures will provide insight into the acute and cumulative effects of tACS on craving regulation and impulse control.

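### Day 15 is meant to show whether behavioural and neural changes persist, but only trait questionnaires and adverse events are named for that day

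*Protocol article*

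**What the plan says.** Section 2.4 closes by giving Day 15 its purpose: "follow-up assessments on Day 15 will evaluate whether observed behavioral and neural changes persist beyond the immediate intervention phase". The next sentence adds: "This longitudinal component is designed to assess the sustainability of tACS effects and explore delayed neuroplastic adaptations".

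The same section defines what the trial is mainly looking for: "The primary outcomes of this study are changes in food craving intensity and inhibitory control following the tACS intervention". Craving is measured by the S-FCQ and FCI, and inhibitory control by a Go/No-Go task.

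The article lists days for each measure:

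- **Primary instruments.** Section 2.5 says they "will be administered pre- and post-stimulation on Days 1 and 5, and again on Day 8 to assess short-term changes in craving".
- **EEG.** Section 2.4: "EEG will be recorded immediately before and after stimulation on Days 1, 5, and 7 to capture neurophysiological aftereffects". Section 2.5 gives the same three days.
- **fMRI.** The Figure 1 caption: "Post-intervention imaging (fMRI) and follow-up behavioral measures occur on Day 8". Section 2.5 lists Days 0, 2 and 8.
- **T-FCQ and YFAS 2.0.** Section 2.5 says these "will be administered at baseline (Day 0) and again during the follow-up session on Day 15 to examine long-term or sustained effects".

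The Figure 1 caption mentions a Day 15 assessment for sustained effects and adverse events, without naming an instrument.

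**The concern.** To show that an observed change persists, the variable in which it was observed must be measured again later. If an active arm lowers S-FCQ scores or alters connectivity by Day 8, the reader of Section 2.4 expects Day 15 to show whether that is still so. As scheduled, Day 15 contains none of those variables.

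The risk is one of interpretation. A T-FCQ or YFAS 2.0 result at Day 15 could be reported as evidence that the primary or neural effects lasted, or did not last, although those outcomes were not measured then. Once participants have passed Day 15, the missing measurements cannot be recovered.

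**Working it through.** No sample size, power or error-rate figure bears on this point, so the check sets the stated schedule against the stated purpose. The days come from Sections 2.4 and 2.5 and the Figure 1 caption.

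| Measure | Role | Days stated | Last day | On Day 15? |
|---|---|---|---|---|
| S-FCQ | primary | 1, 5, 8 | 8 | no |
| FCI | primary | 1, 5, 8 | 8 | no |
| Go/No-Go | primary | 1, 5, 8 | 8 | no |
| EEG | secondary, neural | 1, 5, 7 | 7 | no |
| fMRI | secondary, neural | 0, 2, 8 | 8 | no |
| T-FCQ | secondary, trait | 0, 15 | 15 | yes |
| YFAS 2.0 | secondary, trait | 0, 15 | 15 | yes |

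Section 2.4 gives only Days 1 and 5 for the primary instruments and only Days 0 and 8 for fMRI. The table uses the fuller lists in Section 2.5. The difference does not affect the Day 15 column.

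**Count on Day 15.** Primary instruments 0 of 3; neural modalities 0 of 2; trait questionnaires 2 of 2.

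**Distance from the last session.** Daily stimulation ends on Day 7. The last primary measure and the last fMRI come 8 − 7 = 1 day later, and the last EEG is on the same day (7 − 7 = 0). Day 15 is 15 − 7 = 8 days later. The interval in which persistence would be judged therefore contains no primary or neural measurement after its first day.

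**What the trait questionnaires can show.** With values on Days 0 and 15 only, they give the net change from baseline to 8 days after the last session. Compared between the active and sham FA+ arms, that is a valid estimate of a trait-level effect at Day 15. With no value in between, they do not show whether an earlier post-treatment change was kept. They also measure something other than the state scales: the Discussion itself separates lasting trait tendencies from momentary craving.

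**Whether the analysis text fills the gap.** Section 2.5 gives the craving ANOVA a time factor with two levels, pre and post, and no follow-up level. The only named model for measures taken on Day 15 is the hierarchical linear regression for YFAS and T-FCQ. Schedule and analysis therefore agree with each other, and both fall short of the purpose stated in Section 2.4.

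**The case against.** The strongest reply is that Day 15 does address durability. The T-FCQ and YFAS 2.0 are listed as outcomes, Section 2.4 says they may be modulated by tACS, Section 2.5 assigns them to sustained effects, and they have their own longitudinal model. This stands. A reader might infer that the trial has no Day 15 data on any outcome in which it seeks an effect, or that durability cannot be studied at all. The article does not support either reading. What is out of reach is narrower: persistence of change in the primary behavioural outcomes, EEG and connectivity.

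Three further replies carry some weight.

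- **The schedule is not stated to be exhaustive.** The Figure 1 caption names no Day 15 instrument, the figure itself is not available, and Section 2.5 introduces the two trait scales as examples of a broader set. That the primary measures are absent is inferred from their listed days. The inference is nevertheless firm, because explicit days are given for every primary and neural measure and Day 15 is never among them. For the same reason this is a conflict within the article and not a detail left to a fuller document.
- **Durability is acknowledged as a limitation.** The Discussion calls for longer studies of it, but attributes the limitation to the short course of stimulation. It does not say that these outcomes go unmeasured on Day 15, and the promise in Section 2.4 remains.
- **Durability is not the primary aim.** This is correct. It limits the weight of the point and makes a wording-only correction acceptable.

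**Conclusion.** The point holds in limited form. Section 2.4 promises a Day 15 assessment of persistence that the stated schedule and analyses cannot deliver for any of the 3 primary instruments or either of the 2 neural modalities. A trait-level active-versus-sham difference 8 days after the last session can be estimated. The pre/post comparison of the primary outcomes is unaffected.

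This rests on two assumptions: that the days listed for each measure are complete, and that the last of the seven daily sessions falls on Day 7, as the Figure 1 caption states. The correction should be made, but it does not threaten the trial's main result.

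**What to change.** **Preferred.** Add the S-FCQ and FCI to the existing Day 15 follow-up in Sections 2.4 and 2.5 and in Figure 1. Add Go/No-Go as well if that session is held in person. Analyse Day 15 as a further time point, and name the Day 15 active-minus-sham difference among the randomised FA+ arms as the durability estimate. In Section 2.4, remove the reference to neural changes and to delayed neuroplastic adaptation, since no neural measurement is planned for that day.

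**Minimum.** If the measures are not added, restrict the Day 15 objective to trait craving, food-addiction score and adverse events. This costs only wording and removes the contradiction, but leaves persistence of the primary outcomes unstudied.

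**Cost.** The two questionnaires add a few minutes of participant burden to a follow-up already planned. The cost of Go/No-Go depends on whether Day 15 is in person, which the article does not state. Section 4 says that final ethics approval and registration will precede enrolment, so the change is cheapest before then.
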